### Safety and adverse events

An independent Data Safety Monitoring Board (DSMB) will evaluate the safety data in the context of the overall trial and the currently existing information about the study drug. The DSMB is composed of three experts in their respective disciplines of medicine, clinical trial methodology and conduct.

The DSMB will review the data during the course of the study, a charter delineating their guidelines for operating and stopping rules for terminating individual patients, a portion or all of the trial prematurely, was drawn up before the trial started. The members of the DSMB, meeting plan and responsibilities are specified in the original protocol (p.8, 42–43).

The definition, handling, follow-up and reporting of AEs are defined in the original protocol (p.34–38).

### Statistical analysis

*Power calculation*: the primary endpoint ICU admission is defined by criteria for selection for ICU. We have assumed that 50% of the subjects will have at least one criterion during the course of the study and we aim to reduce the ICU admission rate by 40%, that is, to an ICU admission rate of 30%. To achieve 80% power with type-I error rate of 0.05 (two-tailed), a sample size of 93 subjects per group is required. We plan to enrol 200 subjects into this trial. Interim analyses may decide to recalculate sample-size for the trial.

Sample size calculation was done in nQuery V.7.

Primary and secondary endpoints will be evaluated using the intent-to-treat population (ie, all randomised subjects) and the primary endpoint also using the per protocol population (ie, all randomised subjects with no major protocol violations). All randomised subjects will be included in the safety population. The primary analysis of the primary endpoint will be performed using the Cochran Mantel Haenszel test adjusting for randomisation strata site and gender.

### Patient involvement

The study design and consent form were discussed with and approved by a patient representative. We thank [name], patient contact at Rare diseases Sweden for her support.

## Limitations

The current trial has limitations and there are several potential threats to the validity and generalisability of the results. First, due to the nature of the epidemic, available resources, the risk of transport and contamination, it would be unethical and possibly unsafe to conduct a placebo-controlled trial. Second, ‘Best practice’ have changed over the course of the pandemic and it may differ between different countries and centres. In the evaluation of safety and efficacy these aspects will be considered. Third, the sample size calculation and risk factors are based on early pandemic data. The rationale for 1:1 randomisation is that this is a new disease and we will use a slightly lower dose than often used in more stable patients without ALI. Also, 1:1 allocation will maximise the statistical power. If the interim analysis can show supportive evidence for efficacy, the trial committee/safety and data monitoring board may choose to change the randomisation to 2:1.

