### Randomisation

Subjects will be enrolled and randomised consecutively as they are found to be eligible for inclusion in the study. HBO treatment will start within 24 hours of randomisation. Eligible subjects will be randomised in a 1:1 allocation, stratified by site and gender in blocks (blinded to all but the randomising clinical research associated at Karolinska Trial Alliance, KTA) to either HBO or Control. The randomisation sequence is computer-generated using RANDOMIZE.NET.

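### If allocation moves to 2:1 at the interim, the primary test stratified only by site and gender would confound arm with enrolment period

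*Protocol article*

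**What the plan says.** Allocation starts equal. The Randomisation section states: "Eligible subjects will be randomised in a 1:1 allocation, stratified by site and gender in blocks".

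The Limitations section, after defending 1:1 partly on grounds of power, adds a conditional departure: if the interim supports efficacy, "the trial committee/safety and data monitoring board may choose to change the randomisation to 2:1". No threshold or timing is given.

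The primary endpoint is the proportion admitted to ICU from day 1 to day 30. Under Statistical analysis it is compared in all randomised subjects, "performed using the Cochran Mantel Haenszel test adjusting for randomisation strata site and gender". No other stratum is named.

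The Limitations section also says that best-practice treatments "have changed over the course of the pandemic" and may vary by country and centre. It promises to take this into account when safety and efficacy are evaluated, but names no method. Current trial status reports site openings in May 2020, November 2020 and June 2021, with 31 subjects randomised.

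**The concern.** Under a constant allocation ratio, a change in care over calendar time affects both arms alike and does not bias the comparison. Once the ratio changes, a larger share of the HBO arm than of the control arm is recruited after the change. A test that pools the two phases within each site-by-gender stratum then compares arms with different mixes of early and late subjects. Any difference in background ICU risk between the phases enters the estimated HBO effect.

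The article describes the ingredients itself: an allocation change driven by interim efficacy, a standard of care that moves, and a primary test that does not separate the phases. At stake are the size of the primary test and the direction of the estimated effect. An improving standard of care could be read as a benefit of HBO.

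**Working it through.** **Inputs from the article.** ICU admission 50% in controls and 30% with HBO; two-sided alpha 0.05; power 80%; 93 per group required; 200 planned; 1:1 allocation with an optional move to 2:1; test strata site and gender.

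**Assumptions, not in the article.** Switch after 25%, 50% or 75% of 200 subjects. Background ICU rate falling from 50% to 40%, 30% or 20%, either as a step exactly at the switch or linearly over the 200 subjects. No HBO effect.

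**1. The plan's own figure.** With the pooled-variance formula and mean rate 0.40:

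n = [1.96·√(2·0.40·0.60) + 0.8416·√(0.50·0.50 + 0.30·0.70)]² / 0.20² = (1.358 + 0.571)² / 0.04 ≈ 93 per group.

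This reproduces the article. The sample size is not at fault.

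**2. Imbalance in enrolment period, switch at 100.** HBO has 50 early and 100·2/3 = 66.7 late; control has 50 early and 100/3 = 33.3 late. The late share is 66.7/116.7 = 57.1% for HBO and 33.3/83.3 = 40.0% for control, a gap of 17.1 points. For a switch at 25% the late shares are 80.0% and 66.7%; at 75% they are 30.8% and 18.2%.

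**3. Bias with no HBO effect.** Bias = (late share HBO − late share control) × (late rate − early rate).

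- Step 50% to 30%: 0.171 × (−20) = −3.4 points (HBO 38.6%, control 42.0%).
- Step 50% to 20%: 0.171 × (−30) = −5.1 points.
- Step 50% to 40%: 0.171 × (−10) = −1.7 points.
- Linear 50% to 30%: phase means are 45% and 35%, so 0.171 × (−10) = −1.7 points.
- Linear 50% to 20%: phase means are 42.5% and 27.5%, so 0.171 × (−15) = −2.6 points.

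For a step to 40%, 30% or 20%, a switch at 25% gives −1.3, −2.7 or −4.0 points, and a switch at 75% gives −1.3, −2.5 or −3.8 points. A rising rate reverses the sign.

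**4. Error of the primary test.** Simulation with 200 subjects, six equally likely site-by-gender strata, permuted blocks and 5,000 trials per scenario. The statistic is Z = Σ(aₖ − n₁ₖeₖ/nₖ) / √Σ[n₁ₖn₀ₖeₖ(nₖ − eₖ) / (nₖ²(nₖ − 1))]. Here, in stratum k, aₖ is HBO events, eₖ all events, n₁ₖ and n₀ₖ the arm sizes and nₖ their sum. Rejection is at |Z| > 1.96. Monte Carlo standard error near 5% is √(0.05·0.95/5000) = 0.3 points.

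| Switch at 100, always made, step change | Site and gender | Plus period |
|---|---|---|
| No drift | 4.9% | 4.9% |
| 50% to 40% | 5.5% | 5.0% |
| 50% to 30% | 7.0% | 5.2% |
| 50% to 20% | 10.1% | 4.8% |

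Repeated runs gave 7.0% to 7.6% for the step to 30% and 10.0% to 10.5% for the step to 20%. With a linear fall, the site-and-gender test gave 5.6% to 5.7% (to 30%) and 6.2% to 6.5% (to 20%); a period stratum again brought it to about 5%.

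If the switch is made only when the interim favours HBO by more than one standard error (an assumed rule, met in about 16% of null trials), the overall error with a step is 5.4%, 8.0% and 9.1% for falls to 40%, 30% and 20%. With a period stratum it is 4.4% to 5.1%.

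**5. Why the stratum works.** Within each phase the ratio is constant, so drift inside a phase is unrelated to arm. Only the contrast between phases is confounded, and the stratum removes it.

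**The case against.** **The option is discretionary and unused.** At the reported status 31 subjects had been randomised and the DSMB had advised continuing without modification. This stands: nothing is biased now, and the concern is about what the text permits.

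**Drift is assumed.** The article says care has changed, not that ICU admission has fallen. Entry is limited to subjects with poor oxygenation who are judged likely to need ICU, which may damp drift. Staggered site openings also let the site stratum absorb part of a time trend. This stands as a limit on size. Site strata do not, however, remove drift within a site across the switch.

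**The step is a worst case.** It places the whole change in care at the moment of the switch. A linear fall halves the bias. Accepted, and both are shown.

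**The article is a summary.** An analysis plan or an amendment could add a period term. It could, but that would change the primary test the article names.

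Some stronger readings are tempting but not supported:

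- *That the trial will have inflated error, in HBO's favour.* This needs the switch, within-site drift and a downward direction together.
- *That 27% to 40% of trials that switch would falsely favour HBO.* Figures of that order arise with a step drift and a switch made only when interim z is below −0.84. They condition on trials already leaning towards HBO. That selection alone gives about 11% with 1:1 throughout and no drift, so only the excess is confounding. The overall error under that rule is about 8% to 10% with a step, and 6.7% to 7.5% with a linear fall.
- *That the article plans an unblinded sample-size recalculation with uncorrected alpha.* It says only: "Interim analyses may decide to recalculate sample-size for the trial". It states no method, unblinding or final critical value. The 0.05 is given as a sample-size input, and such rules are commonly left to the full protocol or the DSMB charter.
- *That 2:1 materially costs power.* At 50% versus 30%, power is 82.8% with 100:100 and 81.9% with 117:83.

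**Conclusion.** The point holds as a conditional weakness. As written, using the 2:1 option would tie treatment arm to enrolment period, and the stated primary test would not separate them.

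For a switch at mid-trial and a background fall of 20 or 30 points, the spurious benefit ranges from about 1.7 points (linear, to 30%) to 5.1 points (step, to 20%). Two-sided error ranges from about 5.6% to about 10%. A 10-point step does little when the switch is made regardless of the interim (5.5%). With no drift there is no inflation, and a rising rate would work against HBO.

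These sizes rest on assumed drift and switch timing; the direction of the mechanism does not. The matter should be settled before the option is exercised, but it does not invalidate the design or any data collected so far.

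**What to change.** Before any interim efficacy data are seen, do one of the following:

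- State that, if the allocation ratio is changed, the primary Cochran-Mantel-Haenszel test will be stratified by site, gender and allocation period (before or after the change), so that only subjects randomised under the same ratio are compared.
- Or delete the 2:1 option and keep 1:1 throughout.

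The first costs one sentence and one stratification factor. Error stayed at 4.4% to 5.4% in the step-change and no-drift simulations with the stratum. Simulated power at 50% versus 30%, with a mid-trial switch and no drift, fell from 82.3% to 80.9% (1.4 points), still above the planned 80%. The second costs only the discretion to shift allocation. Timing matters: a stratum added after interim efficacy is known would be a post hoc change to the primary analysis.

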## Ethics and dissemination

HBO has the potential to prevent COVID-19 infection developing into ARDS and multiorgan failure and would then relieve ICU resources and potentially save lives. The nature of the disease with high mortality and no effective cure make the risk group a ‘vulnerable group’ and it is important to make sure that the subjects are not unduly influenced by the expectation or benefits associated with participation. Therefore, the study will be carried out in compliance with ICH-GCP, respective national legislation and according to the Declaration of Helsinki. The National Institutional review board in Sweden (Etikprövningsmyndigheten, Dnr: 2020-01705 Application date 27 March 2020 and approval date 29 April 2020 (included a request for amendment 23 April 2020 and amended 23 April 2020). Approval by the Swedish Medical Product Agency (Läkemedelsverket) (LV: Application 23 April 2020 and decision 8 May 2020), Dnr 5.1-2020-36673. The trial was registered online prior to initiation on ClinicalTrials.gov (31 March 2020), NCT04327505 and on EU Clinical Trials Register (8 May 2020), EudraCT number: 2020-001349-37.

The trial is monitored by KTA, an independent organisation before the trial started, during the trial conduct and after the trial is completed, so as to ensure that the trial is carried out according to the protocol and that data are collected, documented and reported according to ICH-GCP and applicable ethical and regulatory requirements. Monitoring is performed as per the trial’s monitoring plan and is intended to ensure that the subject’s rights, safety and well-being are met as well as data in the eCRF are complete, correct and consistent with the source data. The monitoring will be performed by an independent experienced monitor qualified in ICH-GCP, applicable national and international regulations and the Declaration of Helsinki.

Results will be disseminated at national and international conferences and then published in international peer-reviewed scientific journals with open access. Positive, negative and any inconclusive results will be published.

## Current trial status

The first site was initiated 20 May 2020, second site 29 November 2020, third site 14 June 2021. 31 subjects have been randomised. We conducted the first safety analysis 16/3 when 20 subjects had completed the trial and the first DSMB meeting was conducted 12/5 2021. The DSMB recommended to continue the trial as planned without modifications to the conduct/protocol. We are awaiting a forth wave and plan to initiate more centres during 2021.
